### Study population and study sites

The target population is adults aged 18 years or older diagnosed with early breast cancer as defined by a stage I-III diagnosis (inclusive of ductal carcinoma in situ and locally advanced breast cancer but no distant metastases); within 10 weeks of completion of adjuvant cancer treatment or surgery (if not scheduled for further adjuvant therapy) at a participating cancer centre. Participants will be eligible if they are able to identify a usual GP or GP practice, are ambulatory with an Eastern Cooperative Oncology Group performance status of 0–2 and are able to read and understand English. Cancer survivors will be excluded if they have metastatic breast cancer or the presence of severe mental, cognitive or physical conditions that would limit their ability to participate (as determined by their treating clinicians). Recurrent or secondary primary breast cancer, comorbidities, other prior cancer diagnoses or treatment of trastuzumab (or biosimilars), neoadjuvant and/or ongoing endocrine therapies are *not* exclusion criteria.

The participating cancer centres (clusters) include the Princess Alexandra Hospital (Brisbane, Queensland), Sunshine Coast Hospital and Health Service (Sunshine Coast, Queensland), Gold Coast Hospital and Health Service (Gold Coast, Queensland), Ipswich Hospital (Ipswich, Queensland), Calvary Mater Newcastle (Newcastle, New South Wales) and Canberra Hospital (Canberra, Australian Capital Territory). These centres are large government-funded hospitals that are expected to treat ≥200 people with early breast cancer each year and currently employ at least one breast cancer specialist nurse (BCN). The study opened at all sites in May 2021 and recruitment closed in November 2023. Data collection is ongoing, expected to be finalised in November 2025.

### Study design

The study will employ a SW-CRT design that involves the sequential rollout of the *IBIS-Survivorship* intervention to each of the clusters in a predetermined, randomly allocated order within the study period. Each sequence of treatments per cluster comprises nine cluster periods (see figure 1). In each cluster period (time of measurement), assessments are collected for each cluster and treatment received. All clusters commence in the usual care condition (standard cancer follow-up care), then every 18 weeks (cluster period) one cluster will crossover from usual care to implementation of the *IBIS-Survivorship* intervention. In each cluster, participants who are enrolled in the study prior to the crossover date will be in the usual care arm and will continue to receive usual care. There is no formal transition period, so participants will continue to be enrolled to clusters and receive usual care during the last 8 weeks of that cluster period until the crossover date. Once a cluster has crossed over to the intervention arm, participants enrolled in the study in the following cluster periods will receive the intervention. Thus, participants will not be exposed to both treatment conditions. Enrolment will stop at the end of cluster period seven when all clusters are in the intervention arm. The study intervention delivery will continue for a further two cluster periods (36 weeks) and will formally end when outcome data are collected from the last enrolled participants. The SW-CRT design allows for a staged implementation process which is helpful when simultaneous rollout of an intervention to all clusters is impractical due to logistical and financial constraints.^26^

**Figure 1 F1:**
[figure not shown]
Stepped wedge design schema.

### Participant screening and consent

Research nurses will carry out initial screening to identify potential participants. Potential participants will then be reviewed according to the eligibility criteria by a member of the treating team, and if suitable, asked if they agree to be approached by a research nurse for consent to the study. These potential participants will be provided with a brochure giving detailed information about the study objectives and a Participant Information and Consent Form (PICF) providing details of the study assessments and procedures (online supplemental material B). Participants will be given up to 2 weeks to consider their participation. Participants will provide written informed consent to be enrolled into the trial. All participants will be asked to consent to allow the study team access to their medical record, and a separate written consent form will be used to indicate the participant’s willingness to allow for access to Australian Medical Benefits Schedule and Pharmaceutical Benefits Scheme (PBS) data through Services Australia.

Once a participant consents, this will be recorded in a REDcap^27 28^ database and they will be assigned a unique study ID number. Participants will be automatically invited to complete a baseline survey (T1) on enrolment. This provides sociodemographic information, medical/health history and baseline measures for patient-reported outcomes. If they do not complete this survey within 10 weeks of completion of adjuvant cancer therapies or surgery, the participant will be withdrawn from the study.

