### Intervention

The *IBIS-Survivorship* model of care is a multifaceted intervention that includes a prespecified shared care pathway between oncology specialists and GPs following completion of primary cancer treatment. table 1 outlines the three key activities that comprise the intervention and figure 2 outlines the expected *IBIS-Survivorship* shared care pathway. Activity 1: within 6 weeks to 10 weeks after the completion of active treatment, a 30–60 min consultation between the participant and the BCN is conducted to discuss treatment, provide education and to develop a Survivorship Care Plan (SCP). The SCP will include goal setting of up to three SMART (specific, measurable, achievable, realistic and timely) goals that are developed in partnership between the participant and the BCN, using motivational interviewing and self-efficacy techniques. The initial SCP will be sent to the GP and the participant within 3 days of this consultation. Activity 2: within 4 weeks of the nurse-led consultation, a 20–30 min case conference between the BCN and the participant’s nominated GP is completed to discuss the shared follow-up care schedule, discuss the SCP and negotiate the GP’s role in facilitating the SCP goals. The GP may propose changes or express if they are not willing to take part in specific care activities outlined in the SCP. If a formal case conference is not achievable, a short phone call between the BCN and GP will occur, and if no contact with the GP can be made, a copy of the SCP will be sent to the GP practice records. Activity 3: the participant attends a GP appointment to discuss the SCP, and the shared care follow-up schedule commences consisting of 6 monthly appointments with the oncology specialist team and annual appointments with the GP for up to 5 years post-diagnosis. The GP will be provided with direct telephone access to the BCN in case of concerns or escalation for acute care review. At 5 years, the patient will be discharged to the care of the GP.

**Table 1 T1:** Active ingredients of the IBIS-Survivorship intervention model

Active ingredient	Personnel involved	Specific activities	Note

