	Satisfaction of care	0–10 numerical analogue scale (with 10 being the most satisfied) supplemented with short qualitative interviews.			✓	✓
	Unplanned hospital admissions	Self-report (verified with hospital records)		✓	✓	✓
	Adherence to annual mammogram, physical breast exam and endocrine therapy	Hospital records			✓	✓
Cancer Centre	Reach and representativeness					
	Demographics	Self-report: age, gender, ethnicity, education, living arrangements, marital status, children (including ages) and employment	✓			
	Medical history	Hospital records and self-report: Previous cancer diagnoses and treatments	✓			
	Clinical characteristics	Hospital records and self-report: Breast cancer diagnosis and treatment protocols received	✓			
	Adoption and maintenance (sustainability)					
	% GPs explicit engagement in case conference	Records in database				✓
	Implementation					
	Completion (Y/N) and duration (min) of BCN-led consultation	BCN records, completion of the BCN-led consultation checklist and RN records in database				✓
	Completion (Y/N) and duration (min) of Case Conferencing with GP	BCN records, completion of the GP Case-conference checklist.				✓
	Completed survivorship care plan/components (Y/N)	BCN records, Survivorship Care Plans				✓
	Completed Chronic Disease Management plan (Y/N)	MBS (by GP)				✓
	No. and timing of GP visits and specialist visits	MBS and patient self-report (verified with hospital records)				✓
	Health provider satisfaction	Semistructured interviews				✓
	Economic appraisal					
	Cost-effectiveness	Self-report: The EQ-5D-5L is a standardised measure of health status developed by the EuroQol Group to provide a simple, generic measure of health for clinical and economic appraisal.^55^ The EQ-5D 5 L is a valid, reliable and responsive instrument with published Australian value sets for calculating quality-adjusted life years	✓	✓	✓	

T1=baseline/enrolment; T2=6 months post enrolment; T3=12 months post enrolment.

BCN, Breast Cancer Nurse; CDM, Chronic Disease Management plan; EQ 5D-5L, EuroQol 5 Dimensions 5 Levels; GP, primary care physician; MBS, Medicare Benefits Scheme; RE-AIM, Reach, Effectiveness, Adoption, Implementation and Maintenance.

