### Data collection

#### Patient-reported data

Participant survey data will be collected and managed using REDCap electronic data capture tools hosted at Queensland University of Technology^27 28^ at three time periods (T1 – T3). All participants (intervention and control) will have the option to be emailed a link to online surveys or sent paper-based surveys. If surveys are not completed within 2 weeks of sending, a research nurse will contact the patient to encourage them to complete it.

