### Randomisation and blinding

The unit of randomisation is the cluster. Using the SW-CRT design, each cluster will begin the study as a control site, providing usual care follow-up to participants as per figure 1. An independent statistician randomly generated the order of the clusters, which will be concealed from all investigators and revealed to the cluster investigators 8 weeks prior to the crossover date by the project coordinator. All other clusters will be blinded to the site randomisation. Covariate constrained randomisation was used to balance the number of cluster-periods from a metro and regional cluster across the intervention and control periods. All possible randomisation schemes (720) were simulated. The balance of the randomisation schemes was then scored using the weighted squared difference in the mean values of regional across the intervention and control cluster-periods (where the weight was the inverse variance of the cluster means). A randomisation scheme was selected from the 20% of schemes with the best balance.

During each cluster period, research nurses at each cluster will identify eligible breast cancer patients and invite them to participate in the study. The research nurse recruiting participants will be blind to the randomisation sequence. The randomisation schedule will be kept centrally and only accessible by the project coordinator. The BCNs at each cluster will be informed 8 weeks prior to the crossover date when they will implement the intervention, to allow time for training in intervention delivery. The BCNs will only deliver the intervention to participants enrolled after the cluster’s crossover date. Participants are unable to be blinded and will be informed by their BCN whether they are receiving usual care (control) or *IBIS-Survivorship* care (intervention) at their first clinical appointment following enrolment to the study.

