#### Analysis of effectiveness outcomes

Analyses will be conducted as intention to treat, and clusters will be considered exposed to the intervention postrandomised crossover date. This will include all eligible patients for whom data have been obtained, from enrolment to 12 months. Data will be analysed with respect to the treatment specified for each cluster by the allocated randomisation order.

The primary and secondary continuous outcomes will be analysed using a linear mixed model with an identity link function using a restricted maximum likelihood approximation with a Kenward-Roger approximation which is suitable for small samples.^42 43^ Results will be presented as mean differences between groups with 95% CIs.

The primary outcome will be assessed in a model which will include a random cluster effect, a fixed effect for period (1-9) and a random cluster by period effect to test the difference in means between groups (usual care vs intervention) for FACT-B scores at 12 months. This will estimate the time-averaged effect of the intervention. The random cluster by period interactions will allow for correlations within clusters to decay with increasing separation between times of measurement of observations. Adjustments will be made for the baseline FACT-B scores (as a covariate) and for factors used in the randomisation procedure (metropolitan vs regional location of cancer centre).

Sensitivity analyses will be conducted to estimate the effect of time since exposure, where time since exposure is a fixed effect (1-8). This will assess the effect of the intervention after one period of exposure, two periods of exposure and up to eight periods of exposure compared graphically in forest plots. Additional sensitivity analyses will adjust for patient level covariates (eg, age, education, living arrangement, disease or treatment variable and number of comorbidities) based on expert clinical guidance. The selection of baseline characteristics is based on clinical concern for imbalance between intervention groups or variables that are most prognostic of the outcome.

Similar analyses will be conducted for all secondary outcomes at 6 months and 12 months, including analysis of the difference in means between groups for FACT-B scores at 6 months. Results will be presented as mean differences between groups with 95% CIs.

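### Baseline FACT-B may be completed up to week 10 and the nurse consultation falls in weeks 6 to 10, so some intervention-arm baselines may follow the start of the intervention and still be adjusted for in the primary model

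*Protocol article*

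**What the plan says.** All references are to the protocol article.

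- **Enrolment** (Study population and study sites): patients are eligible "within 10 weeks of completion of adjuvant cancer treatment or surgery (if not scheduled for further adjuvant therapy").
- **T1 invitation** (Participant screening and consent): "Participants will be automatically invited to complete a baseline survey (T1) on enrolment".
- **T1 limit** (same section): "If they do not complete this survey within 10 weeks of completion of adjuvant cancer therapies or surgery, the participant will be withdrawn".
- **Reminder** (Patient-reported data): "If surveys are not completed within 2 weeks of sending, a research nurse will contact the patient to encourage them to complete it".
- **Definition of T1** (footnote to Table 2): "T1=baseline/enrolment; T2=6 months post enrolment; T3=12 months post enrolment".
- **Consultation** (Intervention, Activity 1): the breast care nurse (BCN) meets the participant "within 6 weeks to 10 weeks after the completion of active treatment". Under Randomisation and blinding, only participants enrolled after their cluster's crossover date receive it.
- **Disclosure of arm** (Randomisation and blinding): the BCN tells participants their arm "at their first clinical appointment following enrolment to the study".
- **Primary model** (Analysis of effectiveness outcomes): "Adjustments will be made for the baseline FACT-B scores (as a covariate"). The analysis is described as intention to treat.

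**The concern.** A baseline covariate should be fixed before treatment can act on it. Here the period in which T1 is accepted contains the whole period in which the consultation is delivered, and no stated rule orders the two. The consultation is not a formality: it covers education, goal setting, motivational interviewing and the care plan, and the per-protocol analysis counts it as one of two intervention doses. A FACT-B score given after it may already carry part of the treatment effect. Adjusting for that score removes the same part from the primary estimate. Only the intervention arm has the consultation, so the error does not cancel between arms.

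A second, smaller matter hangs on the same sentence. Enrolled participants are withdrawn for a late T1, although enrolment date has by then fixed their arm and the analysis is called intention to treat.

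**Working it through.** **1. The windows.** Let w be the week of enrolment, counted from the end of treatment. I take completion of active treatment and completion of adjuvant therapy or surgery to be the same date.

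- T1 may be completed from w to week 10.
- The consultation may take place from week 6 (or w, if later) to week 10.
- The overlap is 10 - 6 = 4 weeks, the whole consultation window.
- The reminder falls at w + 2.

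| Enrolled at week | Reminder at week | Position relative to the consultation |
|---|---|---|
| 0 | 2 | Four weeks before the consultation window opens; T1 very likely first |
| 4 | 6 | Reminder falls as the window opens |
| 8 | 10 | Invitation, reminder and consultation share the same two weeks |

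For anyone enrolled from week 4 on, the reminder comes when the consultation may already have happened. The article does not give the distribution of w.

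**2. Direction and size of the shift.** The article states no figure on this point, so there is none to reproduce. The adjusted difference is approximately

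(difference in 12-month means) - β × (difference in baseline means),

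where β is the slope of 12-month FACT-B on baseline FACT-B. Let f be the share of intervention-arm T1s completed after the consultation and e its early effect on FACT-B. The intervention-arm baseline mean is then raised by f × e, and the estimate shifts by

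**shift = -β × f × e.**

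The values of β, f and e are assumptions; none is in the article. The 8-point target and SD of 19 come from its Sample size section and only give the scale.

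| β | f | e (points) | Shift (points) | Share of 8 |
|---|---|---|---|---|
| 0.4 | 10% | 2 | -0.08 | 1% |
| 0.6 | 10% | 2 | -0.12 | 1.5% |
| 0.6 | 20% | 4 | -0.48 | 6% |
| 0.6 | 25% | 4 | -0.60 | 7.5% |
| 0.6 | 50% | 8 | -2.40 | 30% |
| 0.8 | 50% | 8 | -3.20 | 40% |

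In SD units, the shift of -0.60 is 0.60 / 19 = 0.03 SD.

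**3. Check of the formula.** A simulation of 400,000 individuals without clustering used β = 0.6, f = 25%, e = 4 and a true effect of 8. The adjusted estimate was 7.40, which agrees with 8 - 0.60. If no T1 follows the consultation, f = 0 and the shift is 0.

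**The case against.** The strongest reply is that T1 is meant to come first. It is defined as baseline/enrolment, the invitation is automatic at enrolment, a reminder follows after two weeks, and arm is disclosed only at an appointment after enrolment. On this view the week-10 limit repeats the eligibility limit and is just an outer cut-off. The article also condenses a fuller protocol and gives only an overview of the analysis plan. Figure 2, the care pathway, is not shown and may fix the order.

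Much of this stands. T1 will precede the consultation for many participants, so f may be small. It does not remove the point: the article does state a rule for when T1 is too late, and that rule admits a score given after the consultation.

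Three stronger readings are tempting, and the article does not support them.

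- **The primary estimate is badly biased.** A shift of -2.4 points needs half of the intervention-arm T1s to be late. It also needs the full 12-month target effect to appear after one visit of 30 to 60 minutes. At most four weeks can separate a week-6 consultation from the T1 limit, and much of the remaining model is usually still to be delivered by then.
- **The withdrawal rule selects patients differently by arm.** The rule is worded alike for both arms and tied to time since treatment. Reminders come from the research nurse under one procedure for all participants, and nothing says that the BCN prompts T1. Differential withdrawal is possible but speculative, so counting it is enough.
- **Arm disclosure distorts T1 in one arm.** Disclosure is not tied to T1, but it applies to both arms, and the article shows no one-sided effect.

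**Conclusion.** The point holds as a possibility that the stated timing rules leave open. Some intervention-arm baseline FACT-B scores may be measured after the consultation and then adjusted for in the primary model. If the consultation improves early FACT-B, the bias is towards no effect, so it would hide benefit rather than create it.

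The size cannot be derived from the article. With a slope of 0.6, 10% to 25% of intervention-arm T1s late and an early effect of 2 to 4 points, the shift is about -0.1 to -0.6 points, or 1.5% to 7.5% of the target. Larger values need both a large late share and a large early effect. The late share can be counted if both dates are on file, and a count near zero would settle the matter.

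**What to change.** Recruitment has closed, so the remedy lies in the analysis. Fix it before outcomes are analysed by arm.

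1. Compare each intervention-arm participant's T1 date with the consultation date.
2. Define a valid baseline FACT-B as one completed before the BCN consultation.
3. Prespecify a sensitivity analysis of the primary model that does not use later T1 scores as observed baselines and keeps those patients in. The simplest is the same model without the baseline covariate. The alternative is to treat a late T1 as a missing baseline by a method that retains the patient. Because the article plans no imputation, merely blanking the score would drop the patient from the adjusted model. A missing-baseline indicator for late T1s would not help: it would be set only in the intervention arm and would in effect take those patients out of the comparison.
4. Report by arm how many T1s were late and how many participants were withdrawn for not completing T1 in time.
5. Where consent allows, keep outcome data already held on participants withdrawn only for a late T1, in line with the intention-to-treat description. Some may have no T2 or T3 data to keep.

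A joint model of T1 to T3 with a common baseline mean across arms should not be required. Individuals are not randomised and the arms differ in calendar time, so that constraint could itself introduce bias.

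The cost is a date check, a few lines in the analysis plan and one additional model. The downside is a slight loss of precision from using less baseline information.

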#### Clinical data

Information about the participant’s cancer (histology, grade and stage of disease at diagnosis), date of diagnosis and treatment (surgery, chemotherapy and radiotherapy doses and dates) is obtained from medical records at T1 and entered into the REDCap database. Information will be obtained from health service medical records relating to hospital admissions and follow-up appointments including physical breast exam, mammography and endocrine therapy adherence occurring within the first 12 months post enrolment.

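### Withdrawing enrolled participants who miss the T1 survey is a post-allocation exclusion in tension with intention to treat; it matters for record-based adherence outcomes, hardly for FACT-B

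*Protocol article*

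**What the plan says.** All places are in the protocol article.

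- **Enrolment comes first.** Participant screening and consent: "Participants will provide written informed consent to be enrolled into the trial". The survey follows: "Participants will be automatically invited to complete a baseline survey (T1) on enrolment".
- **The arm is set by enrolment date.** Study design: "participants who are enrolled in the study prior to the crossover date will be in the usual care arm". Those enrolled after crossover receive the intervention.
- **A missed T1 ends participation in the study.** Participant screening and consent: "If they do not complete this survey within 10 weeks of completion of adjuvant cancer therapies or surgery, the participant will be withdrawn".
- **The arm is disclosed early.** Under Randomisation and blinding, participants cannot be blinded, and the breast care nurse tells them their arm at the first clinical appointment after enrolment. Under Intervention, the nurse consultation takes place in weeks 6 to 10 after treatment.
- **The analysis is called intention to treat.** Analysis of effectiveness outcomes describes the set as follows: "This will include all eligible patients for whom data have been obtained, from enrolment to 12 months".
- **Some outcomes come from records.** Clinical data: "Information will be obtained from health service medical records relating to hospital admissions and follow-up appointments", including breast examination, mammography and endocrine therapy adherence. Table 2 gives hospital records as the only source for the three adherence outcomes. It gives self-report verified against hospital records for unplanned admissions.

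**The concern.** Whether someone returns a questionnaire is participant behaviour, observed here after the arm has been determined and, for some, after it has been disclosed. Removing people on that basis can unbalance the arms in a way that randomising the crossover order does not prevent.

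People who do not return a survey may also be less adherent to follow-up care. The trial hypothesises that adherence to mammography, examination and endocrine therapy will be equivalent between arms. If one arm loses more of its likely non-adherers, its observed adherence rises for reasons unrelated to care, and a false difference can appear or a real one be hidden. Reach and representativeness would also be described without these people.

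**Working it through.** **1. Order of events**

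| Event | Timing | Section |
|---|---|---|
| Consent and enrolment; arm fixed | Up to week 10 after treatment | Study population and study sites; Study design |
| T1 sent | On enrolment | Participant screening and consent |
| Research nurse prompt | If T1 is incomplete 2 weeks after sending | Data collection |
| Arm disclosed | First clinical appointment after enrolment | Randomisation and blinding |
| Nurse consultation (intervention arm) | Weeks 6 to 10 | Intervention |
| Withdrawal if T1 is missing | Week 10 | Participant screening and consent |

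The exclusion always acts after the arm is fixed. From about week 6 it can also act after the arm is known. For anyone enrolled after week 8 (10 − 2), the deadline passes before the 2-week prompt is due, so some loss is plausible.

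**2. How many people**

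The plan's own figures reproduce: 1384 × (1 − 0.22) = 1079.5 (stated 1079), and 1079 × (1 − 0.30) = 755.3 (stated 755). No stated figure is in dispute. The article gives no T1 non-completion rate. On assumed rates, the number withdrawn out of 1079 would be:

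- 1%: 11
- 5%: 54
- 10%: 108

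**3. Primary outcome**

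The model adjusts for baseline FACT-B, which is collected in T1. Data analysis says missing data will not be imputed. A participant without T1 has no covariate value and leaves the model with or without the rule. The only people the rule itself could remove are those who would have returned T1 after week 10.

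**4. Record-based outcomes**

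Table 2 schedules adherence at T3 and end of study, with no T1 measurement, so a missing T1 does not stop these data from being obtained. Withdrawal from the study would.

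Illustration, with every rate assumed. Let P be true adherence among all enrolled (90% in both arms), q adherence among T1 non-completers (70%), and w the share withdrawn. Adherence among those retained is

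(P − w × q) / (1 − w)

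- w = 10%: (0.90 − 0.070) / 0.90 = 0.9222
- w = 5%: (0.90 − 0.035) / 0.95 = 0.9105
- w = 2%: (0.90 − 0.014) / 0.98 = 0.9041

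| Loss, usual care | Loss, intervention | False difference (intervention − usual care) |
|---|---|---|
| 10% | 5% | −1.2 points |
| 10% | 2% | −1.8 points |
| 5% | 2% | −0.6 points |

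The true difference is zero in each row. If the loss rates were exchanged between arms, the signs would reverse.

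**The case against.** Several points on the other side stand.

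- **A reader might infer a flat contradiction with the intention-to-treat set.** The text does not support that. The set is limited to eligible patients with data, so it does not promise to analyse everyone enrolled. The T1 deadline also equals the 10-week eligibility limit, so T1 may have been meant as an entry condition. As written, however, it acts after enrolment, and the tension remains.
- **A reader might infer bias in the primary result.** With an assumed 10-point FACT-B gap between retained and withdrawn people, 5% loss in the intervention arm against 10% or 15% in usual care gives (0.05 − 0.10) × 10 = −0.5 or (0.05 − 0.15) × 10 = −1.0 point. The rule does not cause this, because people without T1 are lost to that model anyway.
- **Removal from record-based outcomes is inferred.** Participant withdrawal limits observations to the withdrawal date, but it concerns people who decide to withdraw. The full protocol or the analysis plan may settle the matter.
- **Differential loss is possible, not shown.** Research nurses chase surveys in both arms, the breast care nurse informs participants in both arms, and nothing gives that nurse a role in survey return. If nurse contact did improve return in the intervention arm, the resulting bias would run against the intervention.
- **Record coverage has limits.** Participants are asked to consent to record access, which does not establish that all did, and admissions are partly self-reported.

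None of this explains why people whose adherence can be read from hospital records should leave that comparison because they missed a questionnaire.

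**Conclusion.** The concern holds in a limited form. The article states an exclusion that acts after allocation and depends on participant behaviour, alongside an intention-to-treat principle running from enrolment, and the two need reconciling. The consequence for the primary FACT-B analysis is negligible. The practical risk lies in mammography, breast examination, endocrine therapy adherence and the hospital-record part of admissions, if withdrawal from the study means what it says.

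The size and direction of any distortion are unknown. The illustrated 1 to 2 percentage points against the intervention rests on assumed adherence of 90% overall and 70% in non-completers, and on assumed loss of 10% against 2% to 5%. With equal loss and the same kind of non-completer in both arms, the distortion disappears.

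**What to change.** - State that a missed T1 ends survey follow-up only and does not remove the participant from the intention-to-treat set for record-based outcomes.
- Include participants withdrawn under this rule in those outcomes, provided they agreed to record access and have not withdrawn consent.
- Report the number of T1 withdrawals by arm and by cluster period, so that readers can judge whether loss was unequal.

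Making T1 a condition of enrolment is no longer available, since recruitment closed in November 2023. The changes above remain possible while data collection runs to November 2025. They cost some extra record abstraction and possibly an ethics amendment, because Protocol amendments and deviation requires committee approval before a change is implemented. A delta-shift sensitivity analysis of 12-month FACT-B for these people would be a matter of preference and is not needed to resolve this point.
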